### Finite element analysis

A 3D scanner will be used to obtain the geometry of the intact femur and both stems. After modeling the femur, the stems will be placed in the same position as they would be in real surgery. The geometric models of the implanted femurs will be created, based on the orthogonal photographs provided by the cameras during experimental set-up and also the post-implantation antero-posterior and lateral radiographs. Parametric detailed 3D FE models of the bone, the stem and their interface will be developed. Commercially available ANSYS FE code used to develop the femur and implants FE models. For the femur FE model, two different volumes will be meshed to represent the cortical and cancellous material of the bone. Linear tetrahedral elements will be used, as they have been shown to represent smooth surfaces better than cubic hexahedral elements in the femur. Based on a convergence study of the maximum principal strain in FE models with different element sizes (characteristic element lengths: 2 to 10 mm), the optimal element size will be considered. Representative FE models of the cortical and cancellous volumes of the femur are presented in Fig. 4 a, b.

**Fig. 4 Fig4:**
[figure not shown]
(**a**, **b**) Finite element (FE) models of the cortical and cancellous volumes and (**c**) Indicative strain calculated strain field

The FE models, would be first validated against mechanical tests on intact bones. The modeled femurs would be used thereafter to calculate strains and stresses at the whole area of the implanted femurs (Fig. 4c) in order to identify highly stressed areas and areas with stress-shielding phenomenon. These results will be compared to the stresses developed during mechanical testing of the two implanted stems and finally stress results will be compared and associated to the results of the clinical study, especially in terms of implant movement or bone absorption.

### Clinical study

#### Study aims

The main purpose of this study is to compare the functional and radiological results of short-stem THA using the TRI-LOCK BPS and the Minima S Femoral Stem, measured by validated clinical scores including gait analysis and standardized radiological parameters up to a minimum of 2 years’ follow-up.

The primary endpoint will be (1) the incidence of all hip-related complications up to 2 years after surgery and (2) change in health-related quality of life assessed with Western Ontario and McMaster Universities Osteoarthritis Index (WOMAC [44]) and the 36-item Health Survey (SF-36) [45] scores up to 2 years. Hip-related complications are defined as intra- and postoperative fractures, dislocation, wound infection, early or late loosening and revision surgery of any implant for any reason. The secondary endpoints at 1- and 2-years’ outcomes include hip function evaluated with the Harris Hip Score (HHS) [46], the Numeric Pain Rating Scale (NPRS), patient satisfaction [47, 48] and the parameters of gait analysis ((a) gait along a 12-m walkway at the patient’s self-selected normal speed, (b) 12-m gait at high speed in respect to patient’s functional status and (c) the Up and Go Test).

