#### Follow-up assessments

Clinical and radiographic follow-up assessments are scheduled at 3, 6 and 12 months and annually thereafter for a minimum of 2 years’ follow-up. Each visit will include clinical and radiological examination with antero-posterior and frog-leg lateral views of the pelvis. All patients would again fill up the HHS, WOMAC, SF-36 and NPRS scale. At the 1-year appointment and yearly thereafter, patient satisfaction with the results of THA will be assessed and gait analysis will be also performed (Fig. 5).

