##### Statistical analysis

Analysis will be by intention to treat. Differences between groups will be estimated using either the *t* test or Wilcoxon test at the 5% significance level to compare the distribution of the primary endpoint between the treatment samples. The patient outcome scores will be assessed with repeated measures analysis of variance (ANOVA) models to account for the repeated data collection time points. Results will be presented as an adjusted mean difference with its corresponding 95% confidence intervals.

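### Complications, WOMAC and SF-36 are all primary and share one unsplit 5% level, so if any one may carry the primary claim, its false-positive rate is about 9 to 14%, not 5%

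*Protocol article*

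**What the plan says.** All references are to the clinical study part of the Protocol article.

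- **Study aims**, the primary endpoint: "the incidence of all hip-related complications up to 2 years after surgery and (2) change in health-related quality of life assessed with" WOMAC and SF-36. The first of these measures, complications, is one cumulative incidence per arm.
- **Study aims**, second and third primary measures: "change in health-related quality of life assessed with Western Ontario and McMaster Universities Osteoarthritis Index (WOMAC") "and the 36-item Health Survey (SF-36) [45] scores up to 2 years". No visit is singled out, and no SF-36 component or summary score is named. The secondary endpoints in the same section are tied to 1 and 2 years.
- **Follow-up assessments**: "Clinical and radiographic follow-up assessments are scheduled at 3, 6 and 12 months and annually thereafter", for at least 2 years. The scores are completed again at each visit, so there are four postoperative readings by 24 months.
- **Statistical analysis**: a t test or "Wilcoxon test at the 5% significance level to compare the distribution of the primary endpoint between the treatment samples". Then: "The patient outcome scores will be assessed with repeated measures analysis of variance (ANOVA) models to account for the repeated data collection time points".
- **Power and sample size calculation**: 45 per group, from important differences for WOMAC, HHS and SF-36, with an effect size of 0.25 to 0.6 and power of 80% or better. No complication rate is used, and no allowance for several primary tests is stated.

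The article gives no hierarchy, split of the 5%, composite or rule on how many of the three measures must succeed.

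**The concern.** The primary endpoint is written in the singular but holds three separate measures, and the 5% level is attached to it as though there were one test. A difference between the stems on any one measure could be presented as the trial's primary result. The 5% then describes each test and not the trial's main claim. Because the primary visit for the scores is open, there is also a choice of which result to put forward.

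**Working it through.** **Inputs from the article.** Three primary measures; 5% level (two-sided assumed, as sidedness is not stated); four postoperative visits to 24 months; 45 per group; effect size 0.25 to 0.6; 80% power.

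**Assumptions not in the article.** Success on any one measure counts. Correlations between test statistics and complication rates are assumed and shown as ranges.

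**1. The plan's own sample size.** n per group = 2(z₀.₉₇₅ + z₀.₈₀)²/d².
- d = 0.6: 2(1.960 + 0.842)²/0.36 = 43.6, so 44. With the t distribution it is 44.6, so 45. This reproduces the stated 45, for one test at an undivided two-sided 5%.
- d = 0.25: about 252 per group. The 45 therefore belongs only to the upper end of the stated range.

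**2. One test per measure, independent.** 1 − 0.95³ = 1 − 0.857 = **14.3%**. The ceiling under any dependence is 3 × 5% = 15%.

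**3. WOMAC and SF-36 correlated, complications independent.** Let p be the chance that at least one of the two score tests is falsely significant (simulated from correlated normal statistics). The total is 1 − (1 − p) × 0.95.

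| Assumed score correlation | p | At least one false claim of three |
|---|---|---|
| 0.3 | 9.5% | 14.0% |
| 0.5 | 9.1% | 13.6% |
| 0.7 | 8.3% | 12.9% |
| 0.8 | 7.8% | 12.4% |
| 0.9 | 7.0% | 11.7% |

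With all three statistics equally correlated at 0.5, the result is 12.6%.

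**4. Complications by Fisher's exact test.** With 45 per group and assumed true rates of 5% to 20%, the actual size of that test is 0.6% to 2.6%. Put in place of 5% in step 3, with score correlation 0 to 0.7:
- lowest: 1 − (1 − 0.0832)(1 − 0.0057) = 8.9%
- highest: 1 − (1 − 0.0976)(1 − 0.0257) = 12.0% to 12.1% by rounding

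So about 9 to 12%.

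**5. Only if the scores are also tested visit by visit.** Two scores × four visits + one complication comparison = 9 tests. If independent: 1 − 0.95⁹ = 37%. With assumed visit correlations of 0.5 to 0.8 and score correlations of 0.5 to 0.7, simulation gives about 23% to 30%.

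**6. Cost of dividing the level.** 0.05/3 = 0.0167, critical value 2.394. At d = 0.6 and 45 per group, the noncentrality is 0.6 × √(45/2) = 2.846, so power is Φ(2.846 − 2.394) = 67% (66% with the t distribution). At 5% it is Φ(2.846 − 1.960) = 81% (80% with the t distribution). With three tests at 0.0167, the overall error is 1 − (1 − 0.0167)³ = 4.9% if independent.

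**The case against.** **The success rule is not stated.** The error is inflated only if a win on any one measure is enough. If all three had to succeed, it would not be inflated. The article does not say that any one suffices, and the Design section speaks of overall performance. This stands as a condition on every figure above. It does not rescue the plan, because no all-must-succeed rule is stated either, and the sample size makes no provision for complications, which such a rule would need.

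**A larger figure is tempting.** A reader might take three measures at four visits as twelve tests and arrive at 1 − 0.95¹² = 46%. The article does not support this. Complications are one cumulative incidence, so the count cannot exceed nine. Visit-by-visit testing is not stated as the plan either: the repeated measures ANOVA could give one test per score.

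**A floor of 13% is also tempting.** It does not hold. Highly correlated scores or a conservative exact test bring the rate to about 9 to 12%.

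**Detail left to an analysis plan.** A reader might infer that each score is certainly tested twice, by t or Wilcoxon test and again by ANOVA. The text can also be read as a general statement followed by the model for the repeated scores, and which contrast decides is commonly settled in an analysis plan that is not shown. This sub-point carries little weight alone. What the article itself fixes is several primary measures and one unsplit 5%, and that goes beyond missing detail.

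**Ranking is a choice.** Nothing in the article places WOMAC above the other two. Complications come first in the list, and clinical data on the Minima S are said to be lacking. A remedy that simply demotes complications would change a stated objective. This stands, and the fix leaves the choice open.

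**Conclusion.** The concern holds, on the condition that significance on any one of the three measures would be called a primary result. The false-positive rate of the primary claim is then 14.3% with three independent tests, about 12 to 14% for assumed score correlations of 0.3 to 0.9, and about 9 to 12% with a conservative exact test for complications. All of these are roughly two to three times the stated 5%. Rates of 23 to 30%, or 37% under independence, apply only if the two scores are also tested at each visit, which the article leaves open but does not plan. The correlations, complication rates and two-sidedness are assumptions. The three primary measures, the unsplit level and the open visit for the scores are in the text.

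**What to change.** Set 24 months as the primary time for WOMAC and SF-36, name one SF-36 score, and state one deciding model and contrast for each score. Then control the primary error at two-sided 5% in one of two ways:

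- **(a) Fixed order.** Name one confirmatory comparison and test it at 5%. Test the others after it in a stated order, each only if the one before is significant. This needs no more patients and leaves the first test at the full 5%. The later measures lose a stand-alone primary claim.
- **(b) Holm.** Keep all three as primary. No measure is demoted, but at the strictest step (0.0167) power is about 66 to 67% at effect size 0.6 with 45 per group, so the stated 80% would have to be restated. Holding 80% at that step would take about 59 to 60 per group.

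Under either option, report earlier visits descriptively and complications with a confidence interval for the difference between stems.

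The work is mainly wording, but it changes the primary endpoint of a registered trial whose randomization is described in the past tense. It needs a dated protocol amendment and a registry update before outcomes are compared between the groups.

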#### Design

This study uses a prospective, randomized, parallel-group design with blinded treatment and assessment to compare the overall performance of two different short femoral stems, which are theoretically classified in the same main category. This paper is written according to the Standard Protocol Items: Recommendations for Interventional Trials (SPIRIT) 2013 Statement for reporting of clinical trial protocols (Fig. 5, Additional file 1).

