#### Randomization procedures

We used stratified block randomization consisting of a random sequence of blocks of 10 consecutive surgical procedures each. Randomization was performed in the operating theater, after anesthetic induction and just before incision, using a sequentially numbered opaque sealed envelope.

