#### Intervention

All patients will receive the type of implant to which they have been randomly allocated and thus two groups of patients will be created: group A: Tri-Lock BPS group and group B: Minima S Monolithic Femoral Stem implantation group.

The same senior surgeon (PM) will perform all the arthroplasties with a standardized operative technique through a mini-posterior approach. The femur will be prepared in a broach-only fashion and then the prosthesis will be impacted until a tight metaphyseal fit is achieved. The acetabulum will be prepared in a standardized fashion according to the manufacturer’s manual with the intention of using larger femoral heads (28–32 mm). Ceramic or polyethylene inserts and ceramic or metallic heads in respect will be used according to surgeon’s preference and patients age. All patients in both groups will undergo the same postoperative physiotherapy protocol, which consists of gradual progression from up-to-chair tolerance to ambulation and stair-climbing under the supervision of a certified physical therapist. Patients who manage to complete inpatient physical therapy for independent full weight-bearing would be discharged from further therapy but those with less compliance will continue further rehabilitation.

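### The unqualified claim of blinded treatment and assessment cannot hold for the operating surgeon and very probably does not hold for the radiograph readers

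*Protocol article*

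**What the plan says.** The Design section of the protocol article calls the trial a "randomized, parallel-group design with blinded treatment and assessment to compare the overall performance of two different short femoral stems". It names no roles.

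Other sections set out what happens:

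- Randomization procedures: "Randomization was performed in the operating theater, after anesthetic induction and just before incision, using a sequentially numbered opaque sealed envelope".
- Intervention: one senior surgeon "will perform all the arthroplasties with a standardized operative technique through a mini-posterior approach".
- Intervention, on the bearing: "Ceramic or polyethylene inserts and ceramic or metallic heads in respect will be used according to surgeon’s preference and patients age".
- Follow-up assessments: "Each visit will include clinical and radiological examination with antero-posterior and frog-leg lateral views of the pelvis".
- Radiographic evaluation: two examiners, working independently, read all films for fit, alignment, stability, ingrowth and loosening. Intra- and inter-rater agreement is to be measured. Masking to stem type is not mentioned.
- Clinical study, Study aims: the first primary endpoint is the incidence of hip-related complications to 2 years. These are fracture, dislocation, wound infection, loosening, and revision of any implant for any reason. The second is change in WOMAC and SF-36.

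**The concern.** A claim of blinding tells readers how far outcomes are protected from the expectations of those who treat and assess. Here a new stem without clinical data is compared with one that has an established record, a setting in which expectation can shape judgement. If the surgeon and the film readers know the arm, the outcomes that depend on their judgement do not have the protection claimed. Loosening is one of these. Revision may be another, since a decision to revise is ordinarily taken with the films in view.

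A second route is the bearing. If insert and head materials came to differ between arms after allocation, that difference could enter the complication endpoint through dislocation or revision of any implant. The comparison of stems would then be mixed with a comparison of bearings.

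If the wording stands, it is likely to pass unchanged into the results paper.

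**Working it through.** No figure in the protocol bears on this point, so the check sets the sections side by side, role by role.

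1. **Surgeon.** Randomization procedures has the envelope opened before incision. Intervention has the same surgeon do every operation in both arms. Whoever implants a stem knows which stem it is. Blinded treatment is therefore impossible for the person giving it, and no supplementary document could change that.

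2. **Radiograph readers.** Implant systems, Study aims (Biomechanical study) and Discussion describe the Tri-Lock BPS as a straight tapered wedge with a constant neck-shaft angle of 130°. They describe the Minima S as curved, anatomically shaped and side-cut at the tip, with a neck-shaft angle of 134° (standard) or 131° (lateralized). Length alone would not always separate them: the ranges are 95–119 mm and 82–118 mm, which overlap from 95 to 118 mm. Overall shape very probably would. Masking the stem on the film would hide the thing being measured. The readers judge loosening, so the problem reaches the first primary endpoint.

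3. **Clinical and gait assessors.** Follow-up assessments puts clinical and radiological examination in the same visit. Nothing says that films are viewed first, and nothing keeps the assessor from them. These assessors can be blinded, but the stated procedure does not secure it.

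4. **Patients.** Allocation follows anaesthetic induction, so patients need not learn their stem. WOMAC and SF-36 (the second primary endpoint), NPRS and satisfaction are reported by patients and can be protected, provided patients are not told or shown.

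5. **Bearing.** Intervention gives the basis of the choice (surgeon's preference and patient age) but not its timing. Nothing requires the choice to be recorded before allocation is revealed.

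The result by role: not blinded (surgeon), very probably not blinded (readers), blindable but not secured (clinical and gait assessors), blindable (patients). Of the five kinds of event in the complication endpoint, two are most exposed to unblinded judgement: loosening and revision.

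**The case against.** The strongest reply is that the phrase can be read as patient blinding plus blinded functional assessment, both of which are feasible. A journal article may leave the mechanics to the full protocol, and a SPIRIT file is cited that is not shown. This stands in part: silence on roles is not a fault in itself. It does not rescue the unqualified claim, which is untrue for the surgeon whatever other documents say.

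Safeguards also exist. Measurements are made in software and corrected for magnification, there are two readers, and subsidence and angular shift have numeric thresholds. These limit discretion and should be credited. They do not blind anyone. Two readers who both recognise the stem can agree with each other and share the same leaning, and the grading into osseointegrated, fibrous stable or unstable remains a judgement.

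Three stronger readings are tempting and are not supported:

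- A reader might infer that the surgeon chooses the bearing already knowing the stem. The article gives no time for that choice, which may be settled in preoperative planning. Only the absence of a stated safeguard is documented.
- A reader might take it as stated that every film reveals the arm. That is a strong inference from the described shapes, but the article does not say it.
- A reader might try to size the bias by asking how few reclassified events would tip a test with 45 patients per group. The article gives no expected complication rate, and such an exercise would show fragility with few events, blinded or not. It would not measure bias from unblinding.

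**Conclusion.** The claim in the Design section overstates the protection the trial has. That it fails for the surgeon is certain from the text. That it fails for the radiograph readers is very probable, and rests on the assumption that the described differences in shape can be seen on the films. The effect is confined to outcomes that depend on those roles: loosening, revision (assuming the decision is taken by someone aware of the stem) and the radiographic outcomes. The patient-reported primary endpoint can remain protected. The amount of bias cannot be derived from the document, and no number is offered. The bearing is a possible co-intervention difference that the plan does not guard against; there is no evidence that one has occurred.

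The point should be corrected, because the wording misdescribes a primary-endpoint component and the remedy is cheap.

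**What to change.** 1. Restate the Design section: patients and clinical and gait assessors blinded; surgeon and radiograph readers not blinded. Treat loosening and revision as unblinded when interpreting the results.
2. At each visit, collect the questionnaires and HHS, and gait where scheduled, before the films are viewed. Have this done by existing staff other than the operating surgeon.
3. Have the surgeon record the intended insert and head on the theatre form before the envelope is opened, with the choice left entirely to the surgeon. Report the bearing used, and any departure from the recorded intention, by arm.

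The definition of loosening should stay as it is. The Radiographic evaluation section treats its thresholds as prompts for further investigation, and making them the endpoint would alter the endpoint instead of correcting the blinding claim.

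The cost is a less favourable blinding claim, a change in the order of tasks at visits with some attention to who does them, and one line on the theatre form. The article describes randomization in the past tense, so items 2 and 3 may reach only the remaining visits and operations. The wording, and reporting the bearing used by arm, can be put right at any stage.

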**Fig. 5 Fig5:**
[figure not shown]
Time schedule and outcome measurements preoperatively and at 3, 6, 12 and 24 months postoperatively

The study is sponsored by the University of Patras Research Committee (ELKE) (University of Patras Campus, Rio, Greece). Ethical approval has already been obtained from the Ethics Committee of the University Hospital of Patras (approval number: 36/ 02-03-2016) and the patients’ written consent was obtained prior to participation in the study. The decision was published in the Greek Transparency Portal, called “diavgeia” on 22 April 2016, with a unique Internet Uploading Number that is ADA:6ΝΩ346906Γ-Φ6Ω. The study is registered with International Standard Randomised Controlled Trial Number ISRCTN10096716.

